**Infection frequency** will be assessed by a self-developed questionnaire. Participants will be asked to state the number of infection episodes for the following infections during the last 12 weeks: Infections of the upper and lower respiratory tract, gastrointestinal infection with diarrhea, cystitis, and fever higher than 38 °C. The total infection frequency will be the sum of all reported infection episodes. If this sum is lower than the number of stated fever episodes with ≥38 °C, the latter will be used as the total infection frequency. Endpoints will be the mean differences in infection frequencies (total, upper respiratory, and lower respiratory tract infections) between intervention and placebo group at trial week 13–16.

Finally, serum und urine parameters will be measured at every sample collection to evaluate the following secondary endpoints:
Mean difference in levels of total serum 25(OH)D between intervention and placebo group at trial day 12–21 and in trial week 13–16 as well as mean difference in change of levels of total serum 25(OH)D from baseline to trial day 12–21 and from baseline to trial week 13–16.Mean serum 25(OH)D levels > 50 nmol/L in intervention group at trial day 12–21 and in trial week 13–16.Mean differences in levels of biomarkers (white blood cell count (WBC), leukocyte subtype counts (band neutrophils, segmented neutrophils, eosinophils, basophils, lymphocytes, and monocytes), serum CRP, serum uric acid, serum creatinine, serum total cholesterol, serum LDL cholesterol, serum HDL cholesterol, and serum triglycerides between intervention and placebo group at trial day 12–21 and in trial week 13–16 as well as mean difference in change of levels of these biomarkers from baseline to trial day 12–21 and from baseline to trial week 13–16.Mean difference in HbA_1c_ levels between intervention and placebo group at trial week 13–16 as well as mean difference in change of HbA_1c_ levels from baseline to trial week 13–16.Differences in frequency of safety parameters (including hypervitaminosis D, hypercalcemia, hypercalciuria, and renal dysfunction (estimated glomerular filtration rate (eGFR) < 30 ml/min/1.73 m^2^) between intervention and placebo group at trial day 12–21 and in trial week 13–16.Mean differences in levels of safety parameters (including albumin-corrected serum calcium, urine calcium/creatinine ratio, and eGFR) between intervention and placebo group at trial day 12–21 and in trial week 13–16.

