### **Study procedures**

#### Study population

Inclusion and exclusion criteria are listed in Table 1. As there will be no preferences regarding age or sex of the patients to be included and since most non-metastatic CRC patients in Germany undergo in-patient rehabilitation within several weeks after first-line treatment, the approach will ensure high representativeness of this population. Recruitment during rehabilitation was chosen because patients are being admitted as inpatients, usually for 3 weeks, allowing administration of the loading dose under medical supervision to ensure close observation for adverse events.

**Table 1 Tab1:** Inclusion and exclusion criteria

Inclusion Criteria	Exclusion Criteria
• Age ≥ 18 years • Non-metastatic CRC patients (UICC stage I-III) • Within 9 months after surgical removal of tumor • At least 3 weeks in-patient rehabilitation in a cooperating clinic is planned • Sufficient knowledge of the German language and mental capabilities to be able to give written informed consent and comply with the study requirements	• No season adapted vitamin D insufficiency or deficiency (see Table 2 for definition) • BMI > 40 kg/m^2^ • Severe anemia (Hemoglobin < 8.0 g/dl) • Severe renal impairment (eGFR < 30 ml/min/1,73 m^2^ calculated with the CKD-EPI equation [26]) • Hypercalcemia (Albumin-corrected serum calcium > 2.65 mmol/L) • Hypercalciuria (Random urine calcium ≥0.60 mmol/mmol creatinine) • High-dose vitamin D_3_ therapy (≥ 2000 IU daily or similar dosage which corresponds to ≥2000 IU daily) • Therapy with vitamin D analogs • Topical therapy with vitamin D_3_ or vitamin D analogs • Therapy with high-dose calcium supplements (> 1000 mg calcium daily) • Therapy with cardiac glycosides • Hypersensitivity towards ingredients in Dekristol® 20,000/1000 I.E.: peanuts, soy, gelatin, lactose, maize starch or sucrose or ingredients in the placebo capsules (mannitol, silicon dioxide) • Nephrolithiasis with symptoms in the last 12 months • Pseudohyperparathyreodism • Sarcoidosis • Participation in another interventional trial • Pregnancy, planned pregnancy in the next 12 weeks, or lactation • No use of adequate contraceptive measures in women with childbearing potential

Abbreviations: *BMI* body mass index; *CKD-EPI* Chronic Kidney Disease Epidemiology Collaboration; *eGRF* estimated glomerular filtration rate; *UICC* Union for International Cancer Control

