### **Statistical analysis plan**

#### Sample size estimation

The sample size calculation is based on the primary endpoint FACIT-F fatigue subscale. We assume that the FACIT-F fatigue subscale is approximately normally distributed. An increase in the FACIT-F fatigue subscale by three points was found to be a clinically relevant reduction of fatigue [19]. The assumed mean and standard deviation of the FACIT-F fatigue subscale are taken from the representative study of Jones et al. [4], which were 38.5 and 10.8, respectively. With a significance level of 0.05 and 80% power, 205 patients are needed in each group to detect a score difference of three or more points using a two-sample t-test for the mean difference, i.e. 410 patients are required in total. The number of patients to be randomized was calculated assuming a 10% drop-out rate. With these assumptions 500 CRC patients need to be screened and 456 eligible persons randomized to achieve the analyzable sample size of *n* = 410.

Given the annual number of overall 1400 eligible CRC patients reported by the participating three rehabilitation clinics in 2016, recruiting of 456 eligible stage I-III CRC patients should be feasible within 24 months.

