### Statistical methods

All analyses will be done using SAS software version 9.4 or higher. Homogeneity of the treatment groups will be described by comparison of the demographic data and the baseline values of key variables. All statistical tests will have a two-sided significance level of 0.05. Besides, 95% confidence intervals will be estimated for all outcomes in the placebo and verum group.

The primary analysis will test the null hypothesis.

H_0_: The FACIT-F fatigue subscale at week 13–16 is the same in the two groups.

versus the alternative hypothesis.

H_1_: The FACIT-F fatigue subscale at week 13–16 is different in the two groups.

The primary endpoint FACIT-F fatigue subscale will be analyzed with an intention-to-treat approach. The intention-to-treat population will include all randomized study participants with data for the primary endpoint and who did not withdraw consent during the trial. A per-protocol analysis will be done additionally as a sensitivity analysis. The per-protocol population will exclude study participants who meet the following criteria:
Fatigue questionnaire missing at trial week 13–16Error in timing of collection of fatigue questionnaire at trial week 13–16After enrollment, it becomes evident that patient met exclusion criteria at time of recruitment or did not meet inclusion criteria.Incompliance to trial medication (defined as intake of less than 80% of capsules) unless treatment was terminated due to safety reasonsSelf-reported intake of vitamin D or vitamin D analogs in addition to the trial medication.Criteria for discontinuation of study medication were met but study medication intake was continued.

We will test on normal distribution for the outcome FACIT-F fatigue subscale with the Shapiro-Wilks test. If normal distribution can be assumed, the primary test statistic will be the two-sample t-test for the mean difference. If normal distribution cannot be assumed for the FACIT-F fatigue subscale, we will log-transform the FACIT-F fatigue subscale and test for normal distribution once more with the Shapiro-Wilks test. If normal distribution can neither be assumed for FACIT-F fatigue subscale nor log-transformed FACIT-F fatigue subscale, a Wilcoxon Rank-Sum test will be applied. In addition, appropriate 95% confidence intervals will be estimated for the FACIT-F fatigue subscale in the two groups and for the difference in FACIT-F fatigue subscale between the two groups.

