As a sensitivity analysis, a linear regression model will be carried out with FACIT-F fatigue subscale as the dependent variable and treatment group as the independent variable. The linear regression model will be adjusted for all variables named in the subgroup analysis while using some variables continuously instead of categorically (age, hemoglobin levels at screening, 25(OH)D levels at screening, BMI at screening, FACIT-F fatigue subscale at screening, insomnia scale at follow-up and pain scale at follow-up). If appropriate, missing covariate values will be imputed with multiple imputation.

All secondary endpoints with a continuous scale will be analyzed with the same statistical methods as described for the primary endpoint. All dichotomous secondary endpoints will be tested with a Chi^2^ test. AEs will be analyzed with descriptive statistics including frequencies of SAEs.

Lastly, the success of the personalized vitamin D_3_ intervention in raising the serum 25(OH)D level will be evaluated in the intervention group at trial day 12–21. Furthermore, the success of the maintenance dose to maintain sufficient vitamin D status in the intervention group will be evaluated in trial week 13–16. To be successful, the mean 25(OH)D levels in the group with personalized vitamin D_3_ intervention should be higher than 50 nmol/L. This translates into the following test hypotheses:
H_0_: Mean 25(OH)D_personalized intervention_ ≤ 50 nmol/LH_1_: Mean 25(OH)D_personalized intervention_ > 50 nmol/L

To test these hypotheses, we will conduct a one-sample t-test on the mean 25(OH)D levels at a one-sided significance level of 0.025. 25(OH)D levels may be log-transformed if this improves the approximation of a normal distribution (to be tested with a Shapiro-Wilks test).

*Exploratory sub-project: “Determinants of the achieved 25(OH)D levels by the personalized vitamin D*_*3*_*intervention”*

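### The only categorical renal safety endpoint ignores loss from the patient's own screening value, and eGFR and the two calcium measures are compared as levels only, without change from baseline (low severity)

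*Protocol article*

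**What the plan says.** Renal safety is a stated secondary objective (Protocol article, Objectives). Under Outcomes and endpoints it enters the secondary endpoints in three ways.

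- **Event frequency.** The categorical endpoint is "renal dysfunction (estimated glomerular filtration rate (eGFR) < 30 ml/min/1.73 m^2", compared between arms at day 12–21 and at week 13–16. No criterion relative to the patient's own starting value is given. Under Statistical methods, "All dichotomous secondary endpoints will be tested with a Chi^2^ test".
- **Continuous safety measures.** The list gives "Mean differences in levels of safety parameters (including albumin-corrected serum calcium, urine calcium/creatinine ratio, and eGFR) between intervention and placebo group" at the same two time points. Change from baseline is not mentioned for these.
- **Creatinine.** The biomarker item includes "serum CRP, serum uric acid, serum creatinine, serum total cholesterol" and adds the "mean difference in change of levels of these biomarkers from baseline to trial day 12–21", and likewise to week 13–16. Levels and change are also both listed for 25(OH)D and HbA1c.

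The entry limit in Table 1 (Study population) is "Severe renal impairment (eGFR < 30 ml/min/1,73 m^2^ calculated with the CKD-EPI equation [26". Table 1 also has limits for albumin-corrected calcium and urine calcium/creatinine, so all three safety measures must be known at screening. Table 3 and the sampling section confirm that blood and urine are taken then.

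**The concern.** A fixed cut-off makes event status depend heavily on where a patient starts. A fall from 75 to 35 (53%) is not an event, while a fall from 31 to 29 (6%) is. For patients who enter well above the limit, the endpoint records only very large losses.

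The endpoint list is also uneven. Baseline values exist for eGFR and both calcium measures, yet only the biomarkers are compared as change from baseline. The safety comparisons therefore leave out information that the trial already collects.

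At stake is how informative the answer to a stated safety objective will be. A finding of no difference in renal dysfunction could coexist with sizeable declines in some patients that the planned tables would not count. The primary endpoint is not involved.

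**Working it through.** **The plan's own figure.** The only computed design figure is the sample size for the fatigue score: "With a significance level of 0.05 and 80% power, 205 patients are needed in each group". With a difference of 3 and SD 10.8 (Sample size estimation) and "All statistical tests will have a two-sided significance level of 0.05":

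n per arm = 2 × (1.960 + 0.842)² × (10.8/3)² = 203.4, rounded up to 204. The stated 205 agrees within rounding, and power at 205 is 80.3%. For drop-out, 410/0.90 = 455.6, so 456. These figures reproduce but do not bear on the renal endpoint, for which no event rate, power or precision is given. The 205 per arm is carried forward below.

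**Loss that goes uncounted.** The endpoint needs eGFR below 30, so the largest uncounted relative loss from screening value e is (e − 30)/e.

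| Screening eGFR | Largest uncounted loss |
|---|---|
| 35 | 14% |
| 45 | 33% |
| 60 | 50% |
| 75 | 60% |
| 90 | 67% |

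**Levels against change.** The documents give no eGFR SD and no correlation between screening and follow-up, so both are assumed. The detectable difference at 80% power is:

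- levels: 2.802 × SD × √(2/205)
- change: the same × √(2(1 − ρ))

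| Assumed SD | Levels | Change, ρ = 0.5 | Change, ρ = 0.8 | Change, ρ = 0.9 |
|---|---|---|---|---|
| 15 | 4.2 | 4.2 | 2.6 | 1.9 |
| 20 | 5.5 | 5.5 | 3.5 | 2.5 |
| 25 | 6.9 | 6.9 | 4.4 | 3.1 |

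(ml/min/1.73 m².) Change scores gain when ρ exceeds 0.5, break even at 0.5 and lose below it. Adjusting for the screening value multiplies the level figure by √(1 − ρ²) instead, which never exceeds 1. That is why the adjusted form is preferable.

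**Can a mean show a few large declines?** As an illustration, suppose 2% of the vitamin D arm (about 4 of 205) fell from 75 to 35. The binary count stays at 0. The arm mean moves by 0.02 × 40 = 0.8 ml/min. The standard error of the arm difference in levels is SD × √(2/205): 1.5 for SD 15 and 2.0 for SD 20. For change with SD 20 and ρ = 0.9 it is 2.0 × √0.2 = 0.9. Even the more precise mean comparison would not reliably reveal this pattern. Only a per-patient count puts those patients on view.

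**What the binary test can do.** If values below 30 are rare, the chi-square comparison has little power at 205 per arm. On assumed rates (normal approximation) it is 17% for 0.5% v 1.5%, 30% for 1% v 3%, and 38% for 2% v 5%.

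**The case against.** The case for leaving the plan alone has several good points.

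- **The limits are coherent.** A reader might infer that an event cut-off equal to the entry limit is a contradiction. It is not: every correctly enrolled patient starts at 30 or above, so any value below 30 is new. The weakness is only insensitivity at higher starting values.
- **The level comparison of eGFR is sound.** A reader might infer that it also treats large losses as non-events. It does not: it is a comparison of means, every loss enters it, and under 1:1 randomization it is unbiased. Only precision is given up.
- **Creatinine change is already planned.** Since eGFR is estimated from creatinine, mean eGFR change would partly repeat it. This stands for the renal mean. It does not cover the two calcium measures, and it does not count individuals.
- **This is a condensed article.** Shift tables or individual listings may be in the full protocol or SAP. That is fair for their absence here. But the article itself fixes the event definition and gives change from baseline to some measures and not others.
- **The added count is no sensitive test.** Suppose 5% of each arm shows a decline beyond the threshold through ordinary fluctuation, and the vitamin D arm has 4 more such patients: 14/205 v 10/205. The risk difference is 2.0 points (95% CI −2.6 to 6.5, p ≈ 0.40). With no background, 4 v 0 gives p ≈ 0.12 by Fisher's test and p ≈ 0.044 by uncorrected chi-square. This stands, and it is why the count should be descriptive.
- **Other safety review exists.** Adverse events are recorded, the steering committee reviews safety, and visit 2 abnormalities trigger action. This helps, but none of it is a comparison between arms of decline from screening. Adverse event observation also ends with the last dose, before the final sample.

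**Conclusion.** The point holds in a limited form and is of low severity. The categorical renal endpoint misses individual losses of up to 50% from a screening value of 60 and 67% from 90; this is plain arithmetic on the stated cut-off. The three continuous safety measures lack the baseline-referenced comparison that the same list gives to the other biomarkers. For eGFR the cost is precision: 5.5 ml/min detectable for levels against 3.5 or 2.5 for change. That rests on an assumed SD of 20, assumed correlations of 0.8 and 0.9, and 205 analysed per arm; with a correlation of 0.5 or below, unadjusted change brings no gain.

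Two stronger conclusions are not supported. One is that a null renal result is virtually assured: the documents give no baseline eGFR distribution, renal event rate or within-person variation, and patients from 30 upward may enter. The other is that the absence of a data monitoring committee rests on this endpoint: Quality control and assurance justifies it by the character of the product and the indication, without reference to renal results.

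**What to change.** 1. For eGFR, albumin-corrected calcium and urine calcium/creatinine, add the between-arm comparison of change from screening at day 12–21 and week 13–16, preferably adjusted for the screening value. Keep the level comparisons.
2. Report by arm, at both time points, the number of patients whose eGFR has declined from their own screening value by more than a relative threshold that the sponsor prespecifies. Give the risk difference with its 95% confidence interval and label it descriptive. The documents offer no basis for a particular threshold, so none is suggested here.
3. Keep the existing categorical endpoint, and leave entry and stopping criteria untouched.

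The cost is an addition to the endpoint list and a few table rows, with no new samples. The downside is that some counted declines will be ordinary creatinine fluctuation, occurring in both arms, so the count must be read as a comparison between arms and not as a tally of harm.

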### **Study procedures**

#### Study population

Inclusion and exclusion criteria are listed in Table 1. As there will be no preferences regarding age or sex of the patients to be included and since most non-metastatic CRC patients in Germany undergo in-patient rehabilitation within several weeks after first-line treatment, the approach will ensure high representativeness of this population. Recruitment during rehabilitation was chosen because patients are being admitted as inpatients, usually for 3 weeks, allowing administration of the loading dose under medical supervision to ensure close observation for adverse events.

**Table 1 Tab1:** Inclusion and exclusion criteria

Inclusion Criteria	Exclusion Criteria
• Age ≥ 18 years • Non-metastatic CRC patients (UICC stage I-III) • Within 9 months after surgical removal of tumor • At least 3 weeks in-patient rehabilitation in a cooperating clinic is planned • Sufficient knowledge of the German language and mental capabilities to be able to give written informed consent and comply with the study requirements	• No season adapted vitamin D insufficiency or deficiency (see Table 2 for definition) • BMI > 40 kg/m^2^ • Severe anemia (Hemoglobin < 8.0 g/dl) • Severe renal impairment (eGFR < 30 ml/min/1,73 m^2^ calculated with the CKD-EPI equation [26]) • Hypercalcemia (Albumin-corrected serum calcium > 2.65 mmol/L) • Hypercalciuria (Random urine calcium ≥0.60 mmol/mmol creatinine) • High-dose vitamin D_3_ therapy (≥ 2000 IU daily or similar dosage which corresponds to ≥2000 IU daily) • Therapy with vitamin D analogs • Topical therapy with vitamin D_3_ or vitamin D analogs • Therapy with high-dose calcium supplements (> 1000 mg calcium daily) • Therapy with cardiac glycosides • Hypersensitivity towards ingredients in Dekristol® 20,000/1000 I.E.: peanuts, soy, gelatin, lactose, maize starch or sucrose or ingredients in the placebo capsules (mannitol, silicon dioxide) • Nephrolithiasis with symptoms in the last 12 months • Pseudohyperparathyreodism • Sarcoidosis • Participation in another interventional trial • Pregnancy, planned pregnancy in the next 12 weeks, or lactation • No use of adequate contraceptive measures in women with childbearing potential

Abbreviations: *BMI* body mass index; *CKD-EPI* Chronic Kidney Disease Epidemiology Collaboration; *eGRF* estimated glomerular filtration rate; *UICC* Union for International Cancer Control

##### Definition of season-adapted vitamin D insufficiency

Only patients with season-adapted vitamin D insufficiency will be included. This means that the 25(OH)D level cut-off will depend on the month of recruitment. The rationale of season-adapted cut-offs is that only patients having vitamin D insufficiency for the entire year should be included. This is a challenge because people with low 25(OH)D levels in winter usually have a sufficing level in summer. The calculation of the season-adapted cut-offs for vitamin D insufficiency is shown in Table 2. The median 25(OH)D levels by calendar month were derived from the ESTHER study, a population-based prospective cohort study with 25(OH)D measurements for 9585 study participants who were recruited over 2 years in Saarland, a small state with approximately 1 million inhabitants located in south-west Germany [27]. The highest median 25(OH)D level was observed in August with 55 nmol/L. Using the threshold for vitamin D insufficiency of the US American Institute of Medicine [28], the cut-off for vitamin D insufficiency in this month was set to 50 nmol/L. The season-adapted cut-offs in the other calendar months were calculated by subtracting their median difference to August 25(OH)D levels from 50 nmol/L using the following equation:

**Table 2 Tab2:** Season-adapted cut-offs for vitamin D insufficiency by calendar month

Calendar month	Median 25(OH)D [nmol/L]	Difference to median of August [nmol/L]	Season-adapted 25(OH)D cut-off [nmol/L]
January	40	15	35
February	40	15	35
March	40	15	35
April	40	15	35
May	41	14	36
June	50	5	45
July	53	2	48
August	55	0	50
September	53	2	48
October	52	3	47
November	45	10	40
December	43	12	38

Season-adapted 25(OH)D level cut-off month X = 50 nmol/L – (55 nmol/L - median 25(OH)D level month X).

Thus, the cut-offs reflect the natural seasonal variation of the 25(OH)D level of a hypothetical person in Germany with a 25(OH)D level of 50 nmol/L in August, the month during which the study participants had the highest 25(OH)D serum levels. An advantage of using season-adapted cut-offs is a constant recruitment rate of patients with vitamin D insufficiency over the whole year. Otherwise, the majority of the participants would be recruited in winter and only few in summer.

